**Methods:**

We describe a case-control clinical study that will be performed in women between 25 and 70 years of age. Cases will be women diagnosed and surgically intervened of breast cancer (stages I and II). Women with antecedents of cancer or advanced tumor stage (metastasis), or who have received antibiotic treatment within a period of 3 months prior to recruitment, or any neoadjuvant therapy, will be excluded. Controls will be women surgically intervened of breast augmentation or reduction. Women with oncological, gynecological or endocrine history, and those who have received antibiotic treatment within a period of 3 months prior to recruitment will also be excluded. Blood, urine, breast tissue and stool samples will be collected. Data regarding anthropometric, sociodemographic, reproductive history, tumor features and dietary habits will be gathered.

Metabolomic studies will be carried out in stool and breast tissue samples. Metagenomic studies will also be performed in stool and breast tissue samples to ascertain the viral, fungal, bacterial and archaea populations of the microbiota. Quantitation of estrogens, estrogen metabolites and EDCs in samples of serum, urine and breast tissue will also be performed.

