### Study subjects

#### Inclusion and exclusion criteria

In this ongoing case-control study, already registered in ClinicalTrials.gov (Identifier NCT03885648), women’s age will range 25–70 years. Cases will be defined as women diagnosed and surgically intervened of incident breast cancer, stages I and II. Controls will be women surgically intervened of breast augmentation or reduction. Women with antecedents of cancer or advanced tumor stage (metastasis), or who have received antibiotic treatment within a period of 3 months prior to recruitment, or any neoadjuvant therapy, will be excluded of the study. Women with oncological, gynecological or endocrine antecedents and those who have received antibiotic treatment within a period of 3 months prior to recruitment will be also excluded. Controls will be matched to cases by age (± 2 years), category of body mass index and hospital of recruitment.

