#### Sample size

Sample size has been calculated taking into consideration the incidence of breast cancer in Spain, the female population of Andalusia and the formula described by Aguilar-Barojas (2005) [18]. Because of that, the number of breast cancer cases will include at least 100 women, matched with 100 control women subjected to breast reduction or augmentation. Three hospital centers will participate in the recruitment: The Unit of Mammary Pathology, General Surgery Service, University Hospital of Jaén, Spain; the Unit of Mammary Pathology, General Surgery Service, University Hospital Campus de la Salud, Granada, Spain; and Ana Moreno Clinic (Granada, Spain).

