#### Biological samples

Blood, breast tissue, stool and urine samples from cases and controls will be collected. Cases women will be enrolled on the same day of the diagnosis. They will be informed about the goals and procedures of the study and their participation will be requested, and those who accept to participate in the study will sign the informed consent. They will be supplied with a kit containing: 1 thermal bag, 1 freezer block, 1 pair of latex gloves, 1 disposable bedpan, 1 spatula, and 2 disposable plastic containers for urine and stool samples.

The day of the surgery, a blood sample will be taken. Serum will be separated by centrifugation to carry out a thorough biochemical analysis and determine estrogens. Breast tissue samples will be taken during surgery, from a marginal area 3–5 cm apart from the tumor. For controls, samples will be taken from any available breast tissue during breast reduction or augmentation surgery. Both feces and urine samples, from healthy and breast cancer-affected women will be collected the day previous to mammary surgery.

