### Functionality of the intestinal and mammary microbiota

Microbiota functionality will be investigated with a metabolomic study and by evaluating their capacity to damage the DNA of HeLa cells.

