### Statistical analysis

Relative abundance of the microbes will be expressed as median ± range. Differences among microbes will be calculated by the *U*-Mann de Whitney. Intestinal and mammary microbiota clusters will be calculated by an analysis of principal components made with the bioinformatic data. Those data will be normalized between 0 and 1, and the Euclidean distance will be evaluated. A permutation ANOVA (PERMANOVA) will be carried out with the PRIMER 7 software. Finally, a tree diagram will be built for each evaluated group based on the different taxonomic scales.

For metabolomic statistical analysis and data display purposes, any missing values will be assumed to be below the limits of detection, and these values will be imputed with the compound minimum (minimum value imputation). The data will be tested for variance homogeneity, and if there were unequal variances, the data will be log-transformed. The statistical analysis of the data will be performed using Array Studio (OmicSoft, NC, USA) and proprietary software from Metabolon. A t-test for equality of the means will be carried out between the intestinal and mammary microbiota and for each metabolite to determine differences. A *p*-value 0.05 will be considered statistically significant. A one-way ANOVA, assuming homogeneity of variance, will be used to determine whether at least two unknown means are all equal or at least one pair of means is different. In case that the variances were unequal, a Welch-ANOVA will be performed. The false discovery rate (q-value) will be calculated to take into account the multiple comparisons that normally occur in metabolomics-based studies, thus estimating the reliability of the results. A q-value 0.1 will be considered statistically significant.

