The hypothesis of this study is that the risk of breast cancer could be associated with the composition and functionality of the mammary and/or intestinal microbiota. The hypothesis is supported by preliminary studies which suggest that the microbial pattern of women with breast cancer is different than that of healthy women, not only with regards to bacterial types and relative abundance, but also with their functionality (metabolic capacity, ability y to damage DNA, etc.) [27, 37–39]. Exogenous factors such as the exposure to EDCs might contribute to this altered pattern [40, 41]. These circumstances would attribute to the microbiota the possibility of acting as an additional environmental risk factor and a potential prognostic modulator of the disease.

Validation of the hypothesis could translate into new recommendations and guidelines of clinical practice to improve prevention and prognosis of breast cancer, alleviating the burden of this disease. Likewise, a better identification of those patients most likely to efficiently respond to treatment could derive, given the fact that efficacy of immunotherapy against cancer depends on patients’ intestinal microbiota [42, 43]. Finally, interventional clinical studies aimed at shifting the mammary/gut dysbiosis of women affected by breast cancer toward a composition similar to that of healthy women could be designed.

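### The only metabolite test with named groups compares stool with breast tissue, not cases with controls, so it cannot by itself show a difference associated with breast cancer

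*Protocol article*

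**What the plan says.** The metabolomic paragraph of the Statistical analysis section states: "A t-test for equality of the means will be carried out between the intestinal and mammary microbiota and for each metabolite to determine differences". The same paragraph adds a one-way ANOVA, replaced by a Welch ANOVA if variances are unequal, and a q-value threshold of 0.1. It does not name the ANOVA groups. The random forest that follows ranks metabolites by their contribution to a classification, but its classes are not named either. The only analysis there that names breast cancer as the outcome is the logistic regression on tertiles of urinary endocrine disruptors, which does not involve metabolites.

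The hypothesis in the Discussion is that "the risk of breast cancer could be associated with the composition and functionality of the mammary and/or intestinal microbiota"; the Abstract and Background say the same in substance. Metabolomics is one of two stated measures of function: "Microbiota functionality will be investigated with a metabolomic study", alongside a DNA-damage assay in HeLa cells. The Abstract adds: "Metabolomic studies will be carried out in stool and breast tissue samples". Under Biological samples, "Blood, breast tissue, stool and urine samples from cases and controls will be collected", so each woman is to give both specimens. On design, "the number of breast cancer cases will include at least 100 women, matched with 100 control women subjected to breast reduction or augmentation", and "Controls will be matched to cases by age (± 2 years), category of body mass index and hospital of recruitment".

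**The concern.** The question is whether metabolites differ between women with and without breast cancer. The t-test as specified asks whether they differ between stool and breast tissue. Stool and breast tissue can differ chemically for reasons unrelated to cancer, and a disease effect can be present without producing any site difference.

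Followed literally, the metabolites this test flags would describe site or matrix, and could be misread as cancer-associated. If the authors intend a case-control test, leaving the sentence as it stands would make that analysis look chosen after the data were seen. This is a contrast the article states, not a detail it omits.

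**Working it through.** **Inputs from the article.** At least 100 cases and 100 controls (Sample size); stool and breast tissue from every woman (Biological samples); significance at p 0.05 per metabolite and q 0.1 (Statistical analysis). Sidedness is not stated, so two-sided is assumed. The 100 + 100 rests on breast cancer incidence, population size and a cited formula. The article gives no effect size, SD or power from which to reproduce it, and nothing below depends on doing so.

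**Assumptions not in the article.** Equal SDs, standardised effects, and a within-woman correlation ρ between the specimens, varied from −0.2 to 0.7.

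**Step 1: what the site contrast estimates.** Let a metabolite have control means μS (stool) and μB (breast), with case shifts δS and δB. With equal numbers of cases and controls, the expected stool-minus-breast difference over all women is

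(μS − μB) + ½(δS − δB).

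If δS = δB, the disease effect drops out. If the shifts differ, half of their difference is added to the site difference and cannot be separated from it. In neither case does the test isolate disease.

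**Step 2: simulation** (4,000 runs, 200 women, ρ = 0.3).

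| Scenario | Site test, unpaired | Site test, paired | Case v control |
|---|---|---|---|
| 0.5 SD case shift in both specimens, no site difference | 1.9% | 5.6% | about 94% in each specimen |
| No case shift, 1 SD site difference | 100% | not run | 5.2% (stool) |

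The site test misses a disease effect common to both specimens, and rejects every time when there is a site difference and no disease effect.

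**Step 3: pairing.** The variance of the difference in site means is proportional to 2(1 − ρ), whereas an unpaired test assumes 2. Its actual size at nominal 0.05 is therefore 2[1 − Φ(1.96/√(1 − ρ))]:

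| ρ | −0.2 | 0 | 0.2 | 0.3 | 0.5 | 0.7 |
|---|---|---|---|---|---|---|
| Actual size | 0.074 | 0.050 | 0.028 | 0.019 | 0.0056 | 0.0003 |

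An unpaired test would be conservative for positive ρ, anti-conservative for negative ρ, and correctly sized only at ρ = 0.

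**Step 4: what the case-control contrast offers.** Within one specimen type, with 100 v 100 and two-sided 0.05, the detectable difference is

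- 80% power: (1.960 + 0.842) × √(2/100) = 0.396, about 0.40 SD;
- 90% power: (1.960 + 1.282) × √(2/100) = 0.458, about 0.46 SD.

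Power is 81% at 0.4 SD and 94% at 0.5 SD. These figures are per metabolite, before false discovery rate control, and ignore the matching.

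**The case against.** The strongest reply is that the sentence is a drafting slip. Its wording is awkward and may have meant a test within intestinal and within mammary samples. The study is described throughout as case-control, so case status is the natural grouping for the ANOVA and the natural class for the random forest. Comparing gut with breast is also not foreign to the aims, since the Background seeks relations between the two microbiota and their metabolic pathways. All of this is fair. None of it puts a disease term into the one test whose groups are named, and a slip still has to be corrected.

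Four stronger readings are tempting, and the article does not support them.

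- **That the functional hypothesis would go untested.** The HeLa assay is a second measure of function, although it uses bacteria cultured from breast biopsies and so does not cover the gut. The ANOVA and random forest are not excluded as case-control analyses.
- **That all q-values would describe organ differences.** The q-value sentence follows both the t-test and the ANOVA and is not tied to the t-test alone.
- **That the plan treats the two specimens as independent.** The variance check and the ANOVAs suggest it, but the article never says whether the t-test is paired, and a condensed article may leave that to a fuller plan.
- **That power for a disease effect is exactly 5%.** This needs an equal shift in both specimens, no site difference and a correctly sized test. With a site difference the test may reject almost always, for reasons unrelated to disease.

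**Conclusion.** The concern holds in a bounded form. The only metabolomic test with named groups uses a contrast that cannot by itself show an association with breast cancer, and no other metabolomic analysis is stated as cases versus controls. This follows from the text and the algebra in Step 1, and does not depend on any assumed correlation or effect size.

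The simulated percentages illustrate the size of the problem under the stated assumptions (ρ = 0.3; shifts of 0.5 or 1 SD); they do not predict this study's results. The pairing point is conditional: if the test is unpaired it is miscalibrated unless ρ = 0, and with positive ρ the error is lost power, not excess false positives.

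**What to change.** Replace the t-test sentence with a per-metabolite comparison of cases and controls, made separately in stool and in breast tissue, accounting for the matching on age, body mass index category and hospital, and with the false discovery rate control already planned. Name the groups for the ANOVA and the classes for the random forest in the same edit, so that the reader can see which analyses carry the disease comparison.

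If a stool-versus-breast comparison is still wanted, label it secondary and analyse it as paired within woman. Where the question is whether the site difference varies with disease, a mixed model with a site-by-case-status interaction would answer it.

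The cost is a change of wording: no new specimens, assays or participants are needed. The article reports that enrolment and data analysis continue, so the correction should be dated and made before the metabolomic comparisons are run or, if some have been run, with that stated.

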### Quantitation of the exposure to EDCs in urine samples

Analysis of non-persistent EDCs will be carried out by dispersive liquid–liquid microextraction (DLLME) and ultra-high performance liquid chromatography with tandem mass spectrometry detection (UHPLC-MS/MS) as previously described with minor modifications [28, 29]. Briefly, urine samples will be thawed completely at room temperature, centrifuge at 2600 x g for 10 min to sediment particulate matter and 0.75 mL will be taken to carry out the analysis. In order to determine total EDCs amount (free plus conjugated) in urine, each sample will be spiked with 50 μL of enzyme solution (β-glucuronidase/sulfatase) and incubated at 37 °C for 24 h. The treated urine will be placed in a 15 mL screw-cap glass tube and spiked with 30 μL of the surrogate standard solution (1.25 mg/L of BPA-d_16_). Urine will be diluted to 10.0 mL with 5% NaCl aqueous solution (w/v) and the pH will be adjusted to 2.0. Next, 0.75 mL of acetone and 0.75 mL of trichloromethane will be mixed and injected rapidly into the aqueous sample with a syringe. After manual shaking, centrifugation and evaporation of the extract, the residue will be dissolved with 100 μL of a mixture consisting of water (0.1% ammonia)/acetonitrile (0.1% ammonia), 70:30 (v/v), and finally 10 μL will be injected in the LC system. Urinary creatinine concentration (mg/dL) will be determined using an automated colorimetric determination, in the same urine samples in which environmental chemical will be assessed. Because of the relatively constant excretion rate of creatinine into the urine (which makes urinary creatinine concentration inversely proportional to urine flow rate), creatinine adjustment is widely used to normalize analyte concentrations in spot samples for environmental exposure monitoring [30].

Bisphenols [bisphenol A (BPA), bisphenol S (BPS) and bisphenol F (BPF)], parabens [(metylparaben (MeP), ethylparaben (EtP) propylparaben (PrP) and butylparaben (BuP)], benzophenones [(UV filters: benzophenone-1 (BP-1), benzophenone-3 (BP-3) and 4-hidroxybenzophenone (4-OH-BP)] will be determined. Final concentrations will be adjusted for urinary creatinine levels (mg/dl), to account for both urine dilution and body composition, as previously reported [31, 32].

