### Quantitation of urinary concentrations of the parent estrogens and estrogen metabolites

Concentrations of estrone, estradiol and 13 estrogen metabolites [2-hydroxylated estrogen metabolites (2-hydroxyestrone, 2-methoxyestrone, 2-hydroxyestradiol, 2-methoxyestradiol, and 2-hydroxyestrone-3-methyl ether); 4-hydroxylated estrogen metabolites (4-hydroxyestrone, 4-methoxyestrone, and 4-methoxyestradiol); and 16-hydroxylated estrogen metabolites (16α-hydroxyestrone, estriol, 17-epiestriol, 16-ketoestradiol, and 16-epiestriol)] will be determined in fasting spot urine samples, adjusting for urinary creatinine levels (mg/dL). The quantitation of urinary estrogens will be assessed by gas chromatography tandem mass spectrometry using a triple quadrupole analyzer as previously described with minor modifications [33, 34]. Briefly, one mL of urine with 25 μL of internal standards solution will be extracted using C18 SPE cartridge (Sep-Pack C18) previously conditioned with 4 mL of methanol and 4 mL of water. After loading the urine sample, the cartridge will be washed with 4 mL of water. The treated urine will then be evaporated. Three mL of acetate buffer 0.1 M (pH 4.5) and 3 μL of β-glucuronidase will be added to the treated urine after being evaporated, and the mixture will be incubated for 3 h at 55 °C. After cooling to room temperature, pH will be increased to approximately 9.5. Then, samples will be extracted with 6 mL of tert-butyl methyl ether by shaking in a rocking mixer and centrifuged. Finally, the organic layer will be evaporated to dryness under a stream of nitrogen. Two μL of the derivatized extract will be injected in split mode into the GC-MS/MS system. All hormone assessments will be carried out simultaneously to reduce intralaboratory variation.

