Random forest (RF) is a supervised classification technique based on an ensemble of decision trees [35] with several advantages. It makes no parametric assumptions, and variable selection is not needed. It does not overfit, and it is invariant to transformation. In RF analysis, it is not necessary to cross-validate or do a separate test set to obtain an unbiased estimate of the test set error. A “variable importance” measure will be computed to determine which variables (metabolites) make the largest contribution to the classification. The mean decrease in accuracy (MDA) will be used as this metric and will be determined by randomly permuting a variable, running the observed values through the trees, and then reassessing the prediction accuracy. If a variable were not significant, then this procedure will have little change in the accuracy of the class prediction (permuting random noise will give random noise). By contrast, if a variable is relevant for the classification, the prediction accuracy will drop after such a permutation, which will be recorded as the MDA. Thus, the RF analysis provides an “importance” rank ordering for biochemicals [35].

Participants will be grouped into tertiles of urinary EDC levels based on their distributions among the controls. Odds ratios and 95% confidence intervals (CIs) for breast cancer comparing the second and third tertiles with the first tertile will be estimated using logistic regression models. Further, associations of participant characteristics with urinary EDC levels, estrogens and estrogen metabolites and fecal microbiome measures will be evaluated by using general linear models and testing either for differences across categories or for trends across categories. Linear regression models will also be used to evaluate associations of each steroid measure with measures of the diversity of the fecal microbiome, abundance and with taxonomic groups at phylum and family levels, adjusting by covariates.

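### The article gives the metabolite tests two unreconciled significance rules (p 0.05 and q 0.1) and states no multiplicity rule for the taxon, steroid and EDC analyses

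*Protocol article*

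**What the plan says.** All the relevant rules are in the Statistical analysis section of the protocol article.

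- **Metabolites.** After describing a t-test for each metabolite, the text says: "A *p*-value 0.05 will be considered statistically significant". It then adds a one-way ANOVA (Welch if variances differ) and continues: "The false discovery rate (q-value) will be calculated to take into account the multiple comparisons that normally occur in metabolomics-based studies". The paragraph ends: "A q-value 0.1 will be considered statistically significant". Nothing links the two thresholds.
- **Taxa.** "Differences among microbes will be calculated by the *U*-Mann de Whitney". No threshold or adjustment is attached. A PERMANOVA is also planned.
- **EDCs.** Logistic regression gives odds ratios with 95% confidence intervals for the second and third tertiles against the first.
- **Steroids.** Linear models will examine "associations of each steroid measure with measures of the diversity of the fecal microbiome, abundance and with taxonomic groups at phylum and family levels". The urinary estrogen section lists the measures: "Concentrations of estrone, estradiol and 13 estrogen metabolites".

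The article names no primary hypothesis among these analyses and does not label any of them exploratory.

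**The concern.** There are two problems, of different strength.

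The first is a conflict on the page. For the same metabolite tests, two criteria are each declared to define significance. They control different things: p 0.05 limits the error rate of each test, while q 0.1 limits the expected share of false findings among those declared. With hundreds of metabolites they give very different lists. The Trial status section says that data analysis is under way alongside enrolment, so an open choice between the rules could be settled after the results are known.

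The second is the scope of the control. The article recognises multiplicity and ties its remedy to metabolomics. It then describes several other families of tests in some detail without a corresponding rule. If those families were judged one test at a time at 0.05, individual taxa and steroid associations could be reported as findings when chance alone would produce a number of them.

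**Working it through.** The article states no number of tests and no expected number of false findings, so there is no figure of the plan's own to reproduce.

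**Inputs from the article**
- EDCs: 3 bisphenols + 4 parabens + 3 benzophenones = 10 (section on EDCs in urine).
- EDC contrasts: 2 per compound (tertile 2 v 1, tertile 3 v 1).
- Steroid measures: 2 parent estrogens + 5 + 3 + 5 metabolites = 15 (section on urinary estrogens).
- Sites sequenced: 2, feces and breast tissue. The steroid models use the fecal microbiome only.

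**Assumptions, because the article gives no figure**
- Metabolites per matrix: 500 to 1,000.
- Phyla plus families tested, *t*: 10 to 70, the same at both sites.
- Every null hypothesis true.
- q-values computed by Benjamini-Hochberg (the article names no method).
- A 0.05 threshold outside metabolomics. The article does not set one for the taxon or steroid tests; for the odds ratios it is only implied by the 95% intervals.

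**Step 1: metabolites, p rule against q rule**
- Expected chance findings at p 0.05 = m × 0.05. For m = 500: 25. For m = 1,000: 50.
- Benjamini-Hochberg at 0.1, simulated with 4,000 runs of independent null tests: mean 0.128 chance findings for m = 500 and 0.122 for m = 1,000. The chance of any is about 10%.

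**Step 2: the rules can disagree in both directions**
- Take p = 0.01 with m = 500. Benjamini-Hochberg accepts it only if 0.01 ≤ 0.1 × k/500, that is, if at least k = 50 metabolites are declared. Otherwise it is significant by p and not by q.
- Conversely, a metabolite with p > 0.05 passes at q 0.1 only when 0.1 × k/m > 0.05, that is, when more than half the family is declared.

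**Step 3: EDC odds ratios**
- Tests: 10 × 2 = 20. Expected chance findings: 20 × 0.05 = 1.0.
- Chance of at least one, if independent: 1 − 0.95^20 = 0.64.

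**Step 4: taxon, steroid and EDC tests together**
- Tests = 15*t* (steroid by taxon) + 2*t* (Mann-Whitney at two sites) + 20 (odds ratios) = 17*t* + 20.

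| *t* | Steroid by taxon | Mann-Whitney | Odds ratios | Total tests | Expected at 0.05 |
|---|---|---|---|---|---|
| 10 | 150 | 20 | 20 | 190 | 9.5 |
| 25 | 375 | 50 | 20 | 445 | 22.3 |
| 48 | 720 | 96 | 20 | 836 | 41.8 |
| 70 | 1,050 | 140 | 20 | 1,210 | 60.5 |

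The steroid-by-taxon models dominate. Each diversity measure adds 15 more tests, or 15 × 0.05 = 0.75 expected chance findings. Models of participant characteristics are not counted. Correlation between tests leaves the expected counts unchanged but widens their spread.

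**The case against.** The strongest reply is that this is a condensed article. Adjustment for many association analyses is commonly left to the full protocol or analysis plan, and neither is shown. The article does not waive control outside metabolomics; it is silent. It gives no 0.05 threshold for the taxon or steroid tests, and the EDC results are described as estimates with intervals, not as decisions. PERMANOVA gives a global test of composition, so that hypothesis does not rest only on taxon-by-taxon tests. All of this stands, and it limits the second part of the point to saying that no rule is stated here. PERMANOVA does not, however, protect claims about individual taxa.

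Two stronger readings are tempting and not supported. A reader might infer that the families without a rule are far larger than the metabolite family. The article gives no metabolite count, and 500 to 1,000 metabolites in each of two matrices (stool and breast tissue) is 1,000 to 2,000 tests, which can exceed the 190 to 1,210 above. A reader might also infer that dozens of chance findings are to be expected. Reaching 24 needs 17*t* + 20 ≥ 480, so *t* of about 28 or more, with every null true and a 0.05 threshold that the text does not set for most of these tests.

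On the metabolites, p could be meant as the per-test criterion and q as a measure of reliability, or p could belong to the t-test and q to the ANOVA. The text says neither. It attaches the same phrase about significance to both thresholds, and with two groups the equal-variance ANOVA is the same test as the t-test. An unseen plan does not remove a conflict that the article itself writes down.

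**Conclusion.** The metabolite part holds as a contradiction in the text: two significance rules for the same tests and nothing to choose between them. On the assumed 500 to 1,000 null metabolites per matrix, the choice is between about 25 to 50 chance findings and about 0.1. Following the p rule would defeat the article's own purpose in computing a q-value.

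The second part holds in limited form. False-discovery control is written for metabolomics only, and this article states no multiplicity rule for the taxon tests, the 15-steroid models or the 20 EDC odds ratios. The figure of about 10 to 60 chance findings is conditional on 10 to 70 taxa, all nulls true and reading every test at 0.05. The EDC odds ratios contribute only about one of these, with a 64% chance of at least one if the tests are independent. It does not follow that the study as a whole lacks control for these families.

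**What to change.** In the Statistical analysis section:

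1. Make q<0.1 the only decision rule for metabolites, applied within each matrix, and name the method (for example Benjamini-Hochberg). Remove p 0.05 as a criterion and report unadjusted p-values as descriptive.
2. Declare the other families and apply the same control in each: taxon tests per site and taxonomic level, and the steroid-by-microbiome models.
3. For the 20 EDC odds ratios, either apply the same control or label them exploratory and report them as estimates with intervals.
4. If the full plan already sets rules for these families, a sentence saying so is enough for items 2 and 3.

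The cost is one paragraph of wording and usually fewer nominally significant results. Where most effects in a family are real, q<0.1 can admit some p-values above 0.05, so the list need not always shrink. No extra data or recruitment is needed.

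### The plan's statements that random forest does not overfit and needs no validation do not hold in general for matched pairs, and its metabolite ranking has no null reference

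*Protocol article*

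**What the plan says.** The Statistical analysis section of the protocol article presents random forest as a supervised classifier for the metabolomic data. It makes two unqualified statements about the method: "It does not overfit, and it is invariant to transformation", and "it is not necessary to cross-validate or do a separate test set to obtain an unbiased estimate of the test set error".

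The measure of variable importance is then fixed: "The mean decrease in accuracy (MDA) will be used as this metric and will be determined by randomly permuting a variable". The stated product is a ranking: "Thus, the RF analysis provides an “importance” rank ordering for biochemicals". The text says that an irrelevant variable will change accuracy little when permuted. It sets no threshold or null distribution for judging what counts as little.

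The design is set out elsewhere in the article. Under Inclusion and exclusion criteria: "Controls will be matched to cases by age (± 2 years), category of body mass index and hospital of recruitment". Under Sample size: "the number of breast cancer cases will include at least 100 women, matched with 100 control women subjected to breast reduction or augmentation". The Methods part of the abstract gives two sample types per woman: "Metabolomic studies will be carried out in stool and breast tissue samples". The random forest text mentions neither the matching nor the two samples, and it does not name the classes to be separated.

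**The concern.** Out-of-bag error is a fair internal estimate when the rows are independent. Here they are not. If the classes are case and control, each woman has a partner of similar age, in the same body mass index category and from the same hospital, who carries the opposite label. A bootstrap that draws single women splits most pairs. A left-out woman is then predicted largely by trees that have seen someone resembling her under the wrong label, which pushes her prediction towards the wrong class. If the classes are stool and breast tissue, the two samples of one woman form the same kind of opposite-label pair.

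The planned importance measure is a drop in this same accuracy. What is at stake is therefore the yardstick on which the ranking is built, and whether a reader can tell a real metabolite from a lucky one. The article also gives a positive reason for doing without further validation, and that reason does not fit its own design.

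**Working it through.** **No figure to reproduce.** The article states no random forest accuracy, error rate, number of metabolites or within-pair correlation. The check is therefore by simulation. From the article come 100 cases, 100 controls and 1:1 matching. Everything else is assumed: 200 metabolites, of which 10 are informative in the runs with signal (shift 0.5 SD); 200 to 300 trees; and, unless stated otherwise, 8 to 20 replicates per setting.

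**Step 1: how often pairs are split.** With n = 200 rows and row-level bootstrapping, given that a woman is out of bag, her partner is in bag with probability 1 − (1 − 1/199)^200 = 1 − 0.365 = 0.635. So in nearly two thirds of the trees that predict a woman, her partner was in the training data.

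**Step 2: no signal, true accuracy 0.50.**

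| Within-pair correlation | Out-of-bag accuracy | Shortfall (points) |
|---|---|---|
| 0 | 0.491 | 0.9 |
| 0.1 | 0.473 | 2.7 |
| 0.2 | 0.446 | 5.4 |
| 0.3 | 0.433 | 6.7 |
| 0.5 | 0.388 | 11.2 |

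Cross-validation that kept pairs together stayed at 0.48 to 0.52. At correlation 0.1, the part due to pairing is only 0.491 − 0.473 = 0.018. A run with five shared pair factors gave 0.479, 0.444 and 0.353 at correlation 0, 0.2 and 0.5.

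**Step 3: a separate pair effect for each metabolite, compared with independent test women.** Bias is out-of-bag accuracy minus true accuracy.

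- No signal: −0.014, −0.036, −0.114 and −0.276 at correlation 0, 0.1, 0.3 and 0.6 (standard errors 0.007 to 0.013).
- Shift of 0.5 SD: −0.043, −0.061, −0.098 and −0.267.
- Pair-grouped 10-fold cross-validation with the shift: 0.658, 0.672 and 0.664 against true 0.686, 0.686 and 0.710 at correlation 0, 0.3 and 0.6, which is short by 0.028, 0.014 and 0.046. Most of the pairing bias goes, though not every shortfall.

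**Step 4: partners share only three matching factors.** This is closer to the stated matching. The factors explain 0%, 10% or 30% of metabolite variance.

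- No signal: −0.010, −0.032 and −0.065 matched, against −0.019, −0.016 and −0.007 unmatched.
- Shift of 0.5 SD: −0.037, −0.040 and −0.080 matched, against −0.050, −0.041 and −0.029 unmatched.

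At 10% or less, matching adds little. At 30% it adds 0.065 − 0.007 = 0.058 without signal and 0.080 − 0.029 = 0.051 with signal.

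**Step 5: two samples of one woman as separate rows with the same label.** The bias turns upward: +0.052 and +0.197 without signal, and +0.024 and +0.101 with signal, at within-woman correlation 0.3 and 0.6. The article does not say that samples will be pooled in this way.

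**Step 6: overfitting.** Training accuracy was 1.000 in every setting of step 3, including pure noise with true accuracy 0.50. The forest fits noise completely. Only the out-of-bag step guards against this, so its validity matters.

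**Step 7: the ranking.** In pure noise, 37% to 48% of metabolites had a positive mean decrease in accuracy, so a positive value is no evidence by itself. With signal, 7.6 to 9.0 of the top 10 were truly informative, so on average 10 − 9.0 = 1.0 to 10 − 7.6 = 2.4 were noise. Keeping pairs together did not materially change this count (7.6 against 7.6, and 8.9 against 9.0).

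**The case against.** The case on the other side is substantial, and several parts of it stand.

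- **No accuracy is promised.** A reader might infer that a reported classification accuracy will be wrong. The article plans no reported accuracy, error rate or AUC. Accuracy enters only as the intermediate from which the importance measure is computed. Nor is bias certain, because it depends on a correlation that the article does not give. This stands.
- **No panel is planned.** A reader might infer that top-ranked metabolites will be carried forward and judged on the same women. In a noise-only experiment with 600 metabolites, refitting on the top 30 gave an out-of-bag AUC of 0.80. The article contains no such step and says that selecting variables is not needed, so that figure does not describe this plan. This stands.
- **The direction is conservative.** Pair splitting makes accuracy look too low, which is not the optimism that overfitting suggests. This stands, but a yardstick that is too low can hide a real signal.
- **Unnecessary is not forbidden.** The article does not prohibit validation or a permutation null. This stands.
- **The order is not shown to change.** No run showed that pair splitting reorders the ranking. This stands; the weakness of the ranking is the missing reference.
- **The classes are not named.** This is true, but case against control and stool against tissue both give paired rows with opposite labels.
- **Resampling details belong in a fuller plan.** This would answer a complaint about silence. It does not answer two unqualified statements that the article makes itself.

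**Conclusion.** The two statements are too absolute, and they do not hold in general for the matched design that the article describes. With no signal, out-of-bag accuracy falls short by about nil to 4 points at within-pair correlation 0 to 0.1 (little more than without pairing), by roughly 5 points at 0.2, and by 11 points or more at 0.5. These sizes rest on assumed correlations, 200 assumed metabolites and row-level bootstrapping. If age, body mass index category and hospital explain little of the metabolite variance, the effect is negligible.

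Separately, the importance ranking has no null reference, so chance entries near the top cannot be identified.

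The point deserves correction but does not threaten the study's main conclusions. The same section gives per-metabolite tests with false discovery rate control beside the ranking.

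**What to change.** - Delete the two statements, or limit them to independent rows and to the out-of-bag estimate.
- Name the classes. Resample or cross-validate with both members of a matched pair, and all samples of one woman, always on the same side of the split.
- Give a permutation reference, swapping labels within pairs, for overall accuracy and for each importance value.
- If a reduced set of metabolites is ever evaluated, select it inside the folds.

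The cost is computing time and a few lines of wording, with no change to recruitment, samples or assays. The article says that both enrolment and data analysis are continuing, so the change should be dated and made before the random forest is run.
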